## Methods/Design

### Study design and protocol

The study design is a bicentric, biphasic, randomized, controlled trial, following the CONSORT statement guidelines
[50]. 60 patients will be randomized into an intervention (supervised functional treatment and WBV) or control group (supervised functional treatment). Intervention will take place twice a week at a rate of 30 minutes per session, for 6 weeks. Figure 
1 schematically illustrates the study protocol.

**Figure 1 F1:**
[figure not shown]
**Schematic illustration of the study protocol.** ER = Emergency Department; Dia & Inc & Ran = Diagnosis, inclusion and randomization of patient; Pat. inform = Patient information; T to Treatment = maximum time interval between patient inclusion and first treatment intervention; D = day; W = week; M = month; Red diamond = Patient visits; Green segments = short-term/mid-term analysis.

The study design is in accordance with the recommendations of the Declaration of Helsinki, and was approved by the Ethical Committee of the Medical University of Munich (#315-12) and the Medical University of Innsbruck (#UN4833). The study is registered as a randomized controlled trial (NCT01702597).

### Study centers, population, screening and randomization

The study will be conducted at the Department of Surgery, Medical University of Munich (LMU), Germany, and the Department of Trauma Surgery, Medical University of Innsbruck, Austria. Patients will be screened within the regular emergency unit setting using a standardized algorithm for ankle sprains
[51]. Patients presenting with an isolated, unilateral, acute unstable ankle sprain grade II or III (as defined in Table 
1), aged 18–40 years, will be informed about the study and potential risks before signing the informed consent. In case initial classification is not possible (i.e. patients do not tolerate medical examinations), patients will be invited for a delayed physical examination four to seven days following trauma. Inclusion and exclusion criteria are listed in Table
1. Within seven days, participating patients must be included and randomized by envelope drawing.

### Intervention

All patients will be allowed early mobilization and pain-dependent weight bearing, functional immobilization by orthosis, PRICE (protection, rest, ice, compression, elevation), NSAIDs as well as home and supervised physiotherapy. Patients will receive a standardized handout for home training. Table 
2 outlines the standardized supervised intervention protocol for both groups, taking into consideration the different soft tissue healing phases. The functional treatment protocol was developed based on treatment guidelines published by the Royal Dutch Society of Physical Therapy
[52] and is similar to previous treatment protocols
[53-56]. Patients will receive supervised physiotherapy twice a week for 6 weeks
[57-59] with each session lasting 30 minutes. Patients will be asked to do home exercises according to the handout every second day.

**Table 2 T2:** Detailed treatment protocol

**Lvl**	**Phases**	**Time**	**Symptoms**	**Treatment Goals**	**Physiotherapy:**	**Physiotherapy:**
					**CONTROL GROUP**	**INTERVENTION GROUP**^**1**^
1	Inflam.	0 - 3d	▪ Pain at rest	▪ Reduction of pain and swelling	▪ PRICE	
			▪ Swelling and hematoma	▪ Improvement of perfusion	▪ NSARDs	
			▪ Pain during weight bearing	▪ Partial weight bearing	▪ Pain-dependent weight bearing +/- crutches	
					▪ Pain-dependent mobilization of the foot	
					▪ No tape or brace (due to swelling)	
2	Prolif.	4 - 10d	▪ Foot can actively be put into neutral position	▪ Restoring function	▪ NSARDs	Frequency 10Hz / 16 Hz
			▪ Reduction of swelling	▪ Restoring full weight bearing	▪ Pain-dependent weight bearing +/- crutches	Amplitude: s. below
			▪ Partial weight bearing without complete heel-to-toe movement		▪ Arch of foot / leg axis	Duration: 5min
			▪ Possible fear of movement		▪ Training of symmetrical gait and regular foot strike	Exercises, vibration:
					▪ Exercises to improve ROM, active stabilization, coordination and regular walking pattern	▪ Gymnastic ball, feet parallel to mark 1 or 2, patient rolls forth and back, in order to Flex/Ext. in the upper ankle joint
					▪ Brace	▪ Gymnastic ball, injured foot placed transverse on the WBV platform (ankle in-between mark 0 and 1), patient rolls forth and back, in order to flex/extent in the upper ankle joint
						Exercises, general:
						▪ Pain dependent weight bearing +/- Crutches
						▪ Walking motion training
3	Early Remod.	11 - 21d	▪ Residual hematoma	▪ Improving muscular strength, and active/ functional ankle stability, and ROM	▪ Information on preventive measures (Brace)	Frequency: >10Hz, 18-24Hz
			▪ Normal heal-to-toe movement	▪ Training regular walking pattern and climbing stairs	▪ Exercises to improve balance, ROM, muscle strength, walking pattern, running and climbing the stairs	Amplitude: 1-2,5mm
			▪ Pain and fear of movement under load		▪ Dynamic stability: stepwise increase of training intensity; switching from static to dynamic exercises	Duration: 3 Sets a 3 Min with 2 Min break each
					▪ Guidance for home training	Exercises, vibration:
						1) Dynamic squatting (warm-up)
						2) Dynamic squatting (increasing depth)
						3) Two leg stance with slightly bend knees, slow weight transfer (right ←→ left)
						4) One-leg squatting, transverse to WBV plate +/- support of the non-injured leg
						Exercises, general:
						▪ Guidance for home training
4	Late Remod.	3 - 6wk	▪ No hematoma	▪ Improvement of resistance during walking, running, climbing stairs	▪ Exercises to improve coordination (skipping, jumping, …)	Frequency: >10Hz, 18-24Hz
			▪ Dorsal flexion possible	▪ Improvement of work/sports specific tasks	▪ Stepwise load increase and switching from static to dynamic / from simple to complex / from cyclic to non-cyclic exercises	Amplitude: 2-3mm
			▪ No more pain or fear of movement during sports		▪ Guidance for home training	Duration: 3 Sets a 3 Min with 2 Min break each
						Exercises, vibration:
						1) Dynamic squatting (warm-up)
						2) Side-skipping with flexed knees
						3) Calf raises
						4) Vibration on a tilted surface, elevated leg = uninjured leg
						5) Static squats (45° / 90°); Frequency 18+, Amplitude 2+
						Exercises, general:
						▪ Guidance for home training

Lvl: Level; Phase: Healing phases; d: days; Remod.: Remodeling; Inflam.: Inflammatory phase; Prolif.: Proliferation phase; wk: week; PRICE: Protection, Rest, Ice, Compression, Elevation; NSARDs: Non-steroidal antirheumatic drugs; ROM: Range of motion; min: Minutes; Hz: Herz; mm: Millimeter; WBV: Whole body vibration; Min: Minute.

The intervention group will use a sinusoidal side alternating vibration system (Galileo® Med M Plus, Novotec, Pforzheim, Germany) with a peak-to-peak displacement range from 0–9 with 5–30 Hz acceleration. They will perform similar exercises as the control group on the vibration platform and the overall session duration will be the same. The detailed WBV intervention protocol is presented in the Additional file
1.

Physiotherapists who will receive specific training for the WBV prior to this study will supervise all training sessions.

### Outcome parameters

The in Table 
3 outlined outcome parameters are the most frequently used in ankle sprain literature
[3,22,25]. Neuromuscular impairment will be assessed using a Leonardo Mechanograph GRFP (16 bit, 800 Hz; NOVOTEC Medical GmbH, Germany) and are marked with a * in Table 
3. Each test will be performed following the manufacturer’s instructions, with the patients not having participated in sports 24h prior to data acquisition. Tests will be conducted as soon as tolerated by patient.

**Table 3 T3:** Complete list of outcome parameters

**Primary Outcome parameter (1)**	
(short term; 6 weeks)	
Postural control: Balance Test (Sway Index)*	[numeric, scale]
	
**Primary Outcome parameter (2)**	
(mid-term; 1 year)	
Subjective Instability (Giving-way)	[dichotomous variable]
	
**Secondary Outcome parameters**	
Return to pre-injury level of activity (work, sports)	[dichotomous variable]
Residual pain:	
Pain at rest	[dichotomous variable; VAS]
Pain on weight-bearing	[dichotomous variable; VAS]
Pain during sports	[dichotomous variable; VAS]
Subjective Instability (Giving-way)	[dichotomous variable]
Recurrence	[dichotomous variable]
Objective instability:	
Anterior drawer	[dichotomous variable]
Talar tilt	[dichotomous variable]
Ankle ROM	[numeric, scale]
Postural control: Balance Test (Sway index)*	[numeric, scale]
Energy/coordination:	
Multiple one leg hopping*	[numeric, scale]
Single two leg jump*	[numeric, scale]
Complications	[text]
Scores:	
Foot and Ankle Disability Index [60]	[numeric, scale]
EQ 5D 5L	[numeric, scale]

### Sample size estimation and statistics

With this study being the first using WBV with acutely injured patients, data to conduct sample size estimation is lacking. Therefore sample size was chosen according to previous studies on WBV or ankle instability
[32,49,61,62].

Statistical methods used will include descriptive statistics, Student’s *t*-test and Fisher’s exact test.

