A neuromuscular training method gaining increased attention is whole body vibration (WBV). WBV involves synchronous or side-alternating sinusoidal vibrations, which are transmitted to the body via platforms. It is believed to evoke muscle contractions via stretch reflexes in the muscle spindle system
[26-28]. A growing body of evidence indicates improvements of various neuromuscular parameters following WBV, such as power, strength, movement velocity, range of motion and balance
[29-38]. Reports to the contrary
[39,40] may be due to heterogeneous patient populations and varying intervention protocols, which in turn can be due to limited knowledge of the dose-effect relationship, i.e. vibration frequency and amplitude.

In general, frequencies <10Hz are believed to loosen muscle and tissue. Frequencies >10Hz and <20Hz still allow active contraction and relaxation of muscle fibers and are used for coordination exercises. Frequencies >20Hz result in isotonic muscle contraction
[41]. Vibration amplitude seems to be positively correlated to muscle activity
[42-44]. Although WBV has numerous contraindications, as listed in Table 
1, the only adverse side effects reported are temporary hyposensitivity of the foot soles
[45].

**Table 1 T1:** Inclusion- and exclusion criteria

**Inclusion criteria**	**Exclusion criteria**
Age: 18 to 40 years	Pregnancy
Acute, unilateral, unstable, inversion ankle sprain (Grade II, III)	Conditions affecting the neuromuscular or musculoskeletal system
Signed informed consent	Previous surgical interventions to the foot, ankle, knee or hip; known FAI, CAI
Patient can read and understand German	Conditions possibly affecting balance
	Cardiovascular disease including thrombosis
	Respiratory diseases
	Abdominal diseases (including gallstones)
	Urological diseases (including kidney and bladder stones)
	Gynaecological diseases and + intrauterine devices
	Neurological diseases including epilepsy within the last 2 years
	Acute injuries to the head
	Patient is not available for follow-up visits
	Patient unable to give informed consent
	Patient suspected to be non-compliant

Functional classification system for lateral ankle sprains: Grade II: hematoma/swelling/pain on palpation and positive anterior drawer test (complete tear of the ATFL, incomplete tear of the CFL); Grade III: hematoma/swelling/pain on palpation and positive anterior drawer test and positive talar tilt test (complete tear of the ATFL and CFL); adapted from

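### The two named tests, Student's t-test and Fisher's exact test, are valid but leave precision unused in a 60-patient trial; ANCOVA with centre and grade, and Boschloo's test, would recover some of it at little cost

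*Protocol article*

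**What the plan says.** The section on sample size and statistics gives the analysis in one sentence: "Statistical methods used will include descriptive statistics, Student’s *t*-test and Fisher’s exact test". It does not say which test goes with which outcome. Table 3 makes the mapping fairly clear: the 6-week primary (Sway Index) is numeric and the one-year primary (giving-way) is dichotomous.

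On size, the same section says that "data to conduct sample size estimation is lacking" and continues: "Therefore sample size was chosen according to previous studies on WBV or ankle instability". It gives no effect size, SD, event rate, significance level, sidedness or power.

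Three other places bear on the point:

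- **Centre.** Study design and protocol: "The study design is a bicentric, biphasic, randomized, controlled trial".
- **Grade.** Table 1 admits "Acute, unilateral, unstable, inversion ankle sprain (Grade II, III"), so grade is established at entry.
- **Sway at other times.** Table 3 lists "Postural control: Balance Test (Sway index") again among the secondary outcomes, without a time point. Under Outcome parameters, testing starts when the patient can tolerate it, so a pre-treatment value is not guaranteed.

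Allocation is described only by the statement that "participating patients must be included and randomized by envelope drawing". No ratio, blocking or stratification is given.

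**The concern.** A two-sample t-test and Fisher's exact test use only the treatment label and the outcome. The trial will hold at least two baseline facts on every patient, centre and sprain grade, that could explain part of the variation in sway. With the size taken from precedent rather than from a power calculation, an analysis that uses this information is a cheap way to sharpen the comparison.

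For the binary outcome, Fisher's test conditions on the total number of events. At about 30 per arm its attainable significance levels are coarse, so the true error falls well below the nominal 5% and power falls with it. An unconditional exact test that ranks tables by Fisher's p-value (Boschloo) keeps the 5% guarantee. It rejects whenever Fisher rejects, so it cannot be less powerful.

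At stake is the chance of detecting a real effect. The validity of a positive result is not in question.

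**Working it through.** **Inputs from the protocol.** 60 patients, two groups, two centres, grade II or III, one numeric and one binary primary outcome.

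**Assumptions, because the protocol does not state them.** Two-sided 5%; 1:1 allocation (30 per arm) as the base case; event rates and covariate correlation as shown below. The figure of 60 cannot be reproduced, since no inputs are given.

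**1. Sway Index, t-test.** With n = 30 per arm, df = 58 and noncentrality d/√(2/30):

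- 80% power needs d = 0.736.
- At d = 0.6, power is 62.8%.

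**2. Sway Index, ANCOVA.** If the covariates jointly correlate r with the outcome, the residual SD is multiplied by √(1 − r²), so d = 0.6 acts as 0.6/√(1 − r²).

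| r (assumed) | effective d | power at d = 0.6 | d for 80% power |
|---|---|---|---|
| 0 | 0.600 | 62.8% | 0.736 |
| 0.1 | 0.603 | 63.2% | 0.732 |
| 0.2 | 0.612 | 64.5% | 0.721 |
| 0.3 | 0.629 | 66.8% | 0.702 |
| 0.5 | 0.693 | 75.1% | 0.637 |

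Two binary covariates reduce the degrees of freedom from 58 to 56. At r = 0 this costs less than 0.1 point of power.

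**3. Giving-way, true size of Fisher's test.** For every possible 2×2 table, mark those with Fisher p ≤ 0.05, sum their binomial probabilities at a common event rate π, and take the maximum over π from 0.005 to 0.995.

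- 30/30: 0.9% at π = 10%, 2.2% at 20%, 2.6% at 30%; maximum 2.74% at 50%.
- Maximum in other splits: 29/31 3.9%; 28/32 3.7%; 27/27 2.6%; 25/25 3.3%.
- The null hypotheses are worded directionally. At one-sided 5% and 30/30 the maximum is 2.8%.

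**4. Giving-way, Boschloo against Fisher.** The Boschloo cutoff is the largest Fisher p-value for which the maximum size stays at or below 5%. At 30/30 it is 0.0692, with maximum size 4.7%. Event rates below are illustrative.

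| Arms | Rates | Fisher power | Boschloo power | Gain (points) |
|---|---|---|---|---|
| 30/30 | 25% v 5% | 43.6% | 52.7% | 9 |
| 30/30 | 20% v 5% | 24.1% | 33.5% | 9 |
| 30/30 | 40% v 15% | 48.9% | 53.4% | 5 |
| 30/30 | 40% v 10% | 70.5% | 74.3% | 4 |
| 29/31 | 25% v 5%, higher rate in the smaller arm | 59.4% | 61.0% | 2 |
| 29/31 | 25% v 5%, higher rate in the larger arm | 47.9% | 56.8% | 9 |
| 28/32 | 20% v 5%, higher rate in the smaller arm | 38.8% | 38.8% | 0 |
| 27/27 | 25% v 5% | 36.1% | 50.0% | 14 |

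Across the scenarios run, the gain lies between about 0 and 14 points.

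**The case against.** The strongest reply is that the sentence is an open list in a condensed article. It says the methods include these tests, and a fuller protocol or analysis plan may add adjusted models. This stands in part. A reader might infer that the trial has decided to ignore centre, grade and earlier sway, and the document does not say so. What remains is that these are the only comparison methods it names, and neither uses covariates.

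Second, both tests are correct for a two-arm randomised comparison, and Fisher's conservatism protects the type I error. This stands in full. A reader might go further and argue that chance imbalance in centre or grade distorts the unadjusted result. It does not bias it: under randomisation the estimate is unbiased, and its standard error already reflects chance imbalance.

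Third, the 2.7% figure is tempting as a general ceiling. It belongs to exactly 30 per arm at two-sided 5%. Envelope drawing with no stated blocking, and possible losses by one year, make other splits likely, and a 29/31 split already gives 3.9%.

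Fourth, the r = 0.5 row is tempting as the expected sway gain, or as a saving in patients. The documents do not support that. A correlation of that size is plausible mainly for a true pre-treatment sway value, and none is fixed. The second listing of sway in Table 3 may refer to a time after the 6-week endpoint, and the Adverse events section expects that some patients may be unable to do load-dependent tests. With centre and grade alone, the gain may be a point or two, or almost nothing.

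Finally, nothing shown says that the sample size could not be changed, so analysis is not the only route to more power. It is a cheap one.

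**Conclusion.** The point holds as an efficiency weakness worth correcting, and as nothing more. The named tests are valid and control type I error.

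- **Giving-way.** Fisher's test runs at no more than about 2.7% (30/30) to 3.9% (29/31) true error in the splits checked. Boschloo's test recovers about 0 to 14 points of power. These figures rest on an assumed two-sided 5% level and illustrative event rates.
- **Sway Index.** At 30 per arm and a difference of 0.6 SD, adjustment raises power from 63% to 63%, 65%, 67% or 75% for r = 0.1, 0.2, 0.3 or 0.5. The correlation is an assumption, and centre and grade alone may sit at the low end.

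**What to change.** Before any outcome data are compared, state the primary analyses as follows.

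1. **Sway Index at 6 weeks.** ANCOVA with treatment, centre and sprain grade. Add an earlier Sway Index only if it was taken before the first supervised session, because a later value is post-treatment.
2. **Giving-way at one year.** Boschloo's exact unconditional test in place of Fisher's, reported with a risk difference and 95% CI. State the significance level and whether the test is one- or two-sided, since the exact cutoff depends on both.

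The cost is a change of wording, a few degrees of freedom and a less familiar exact test. Centre and grade need no new data.

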### Adverse events

The only adverse side effects of WBV reported in literature were temporary hyposensitivity of the foot soles
[45]. Possible adverse events related to the interventions include pain, fall from the WBV device/wobble board, and delayed mobilization or healing. Unexpected events related to data acquisition might be patients’ inability to perform certain load-dependent examinations. Severe adverse events are only expected following a fall from the training device.

## Discussion

The present study protocol on the effect of WBV in patients with acute, unilateral, unstable inversion ankle sprains is the first study to apply WBV in patients with acute soft tissue injuries. Due to its influence on various neuromuscular parameters, which are known to be impaired in patients with ankle instability, WBV provides a novel, functional treatment approach for this problem.

Several limitations of the present protocol must be discussed. First of all, the authors have decided to use a functional classification system. With ankle instability being the most important parameter for further treatment decision, an established functional classification system was chosen. Ankles are classified into stable or unstable based on clinical presentation and examination (swelling, anterior drawer test and talar tilt test)
[46-48]. In case initial examination is not tolerated, delayed physical examination has been shown to be equal to arthrography (specificity/sensitivity: 85%/96%)
[63-65]. Its feasibility in daily practice and high sensitivity makes it a suitable classification system for patients with acute inversion ankle sprains.

Second, as discussed in the introduction, functional treatment seems to be the current gold standard treatment approach. Still, immobilization, as well as type and duration of physiotherapy are a matter of discussion. Kerkhoffs et al.
[66] conducted a systematic review on the effectiveness of various braces/bracing methods for acute ankle sprains and found lace-up supports to be the most effective, which seems supported by a Cochrane Review
[3]. A recent single-blinded RCT by Lamb et al.
[67] found a short period of immobilization in an Aircast brace to result in faster recovery than double-layered tubular compression bandage. This is in line with a review by Kemle et al.
[23] who found evidence pointing towards the superiority of ankle braces. Consequently, initial immobilization will be realized with an ankle brace. Moreover, the type and duration of functional rehabilitation remains unclear. Our supervised rehabilitation protocol is based on the guidelines of the Royal Dutch Society of Physical Therapy
[52], which is comparable to other published treatment protocols
[53-57,68]. Although the optimal intensity of physical rehabilitation remains unclear, 45 minutes, twice to three times a week over a period of 6–8 weeks seem to be beneficial
[10,57-59,69]. Due to administrative issues, we decided on supervised rehabilitation for 30 minutes, twice weekly for 6 weeks, with additional home exercises.

A third possible limitation are the chosen outcome parameters. Whereas power, assessed by a single leg vertical jump, has been proven significantly different between patients with recurrent ankle sprains and healthy controls
[14,70-72], there is no consensus in literature as to which method best assesses balance. A commonly used method is center of pressure (COP)
[73-76]. Whereas COP assessed during single leg stance with eyes open was ineffective in identifying patients with ankle instability
[73,74], this could be achieved with single leg stance with eyes closed
[75,76]. Furthermore, COP provides an objectively verifiable parameter. Other commonly used outcome parameters such as return to work or return to sports are parameters not necessarily coinciding with the recovery of the injured ankle. They highly depend on the patient’s attitude attitude, schedules and type of job/sport.

## Abbreviations

WBV: Whole Body Vibration; PRICE: Protection, Rest, Ice, Compression, Elevation; NSARDs: Non-Steroidal Antirheumatic Drugs; %: Percent; ATFL: Anterior Tibio-Fibular Ligament; FAI: Functional Ankle Instability; CAI: Chronic Ankle Instability; Hz: Herz; ROM: Range Of Motion; RCT: Randomized Controlled Trial; n: Number; H_0_: Hypothesis; h: Hour; COP: Center Of Pressure.
